***Statistical methods:***

Analysis for differences over time for treatment efficacy, AEs, symptom- and examination score, impact on vaginal lactobacilli and relapses will be analyzed for all randomized patients (i.e. intent-to-treat ITT). Additionally, we will also examine efficacy for the per-protocol (PP) population. Four time points will be used to study the efficacy (proportion of participants with negative cultures for *Candida albicans*) in each treatment arm (baseline, 1w post-treatment, follow-up 3 and 6 months). We will examine the difference in means, proportions and median values using 95% confidence intervals (CI). The CI interval will be computed using 1) for a proportion in one sample and 2) logistic or multinomial logistic regression analysis.

Differences in baseline characteristics between the CHG and FLZ groups will be analyzed with Chi2 for categorical data, Mann Whitney U test for ordinal data, or t-test for continuous data to examine potential selection bias at randomization. Differences in drop-out rates across treatment arms will also be analyzed using Mann Whitney U test.

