## Overall study design

The study is a 6 months clinical Phase II trial to compare if 1% chlorhexidine gluconate vaginal cream (Hibitane®) is at least as effective and safe as fluconazole (reference treatment) for culture-verified recurrent vulvovaginal candidiasis. The study is a randomized open non-inferiority trial with parallel treatment groups. The trial is not possible to blind for neither participants nor investigators due to the differences between study treatments. There is low risk of bias since the primary outcome variable is objective (negative vaginal culture for *Candida albicans*).

The rational for the study is to find an alternative treatment to fluconazole for RVVC with high tolerability and without cytotoxic effect on epithelial cells and negative impact on the vaginal microbes.

The participants will be randomization to;

- Investigational medication with Hibitane® vaginal cream 8 ml every night for a week and then prophylactic treatment with 8 ml/week for another 11 weeks

or

- Reference treatment with Fluconazole® 150 mg (oral capsule) every 3 days for the first 3 doses, then prophylactic treatment with 150 mg/week for another 11 weeks

Please see section 7 for more details on randomization and study treatments.

Figure 1 Study design

| **Visit** | **1** | **2** | **3** | **4** | **5** |
| --- | --- | --- | --- | --- | --- |
|  |  | CHG | Chlorhexidine gluconate  vaginal application  8 ml/w, 11 w | |  |
|  |  | 8 ml/day,1 w  R |  |  | N=30 |
|  |  |  | Fluconazole  oral capsules  150 mg/w, 11 w | |  |
|  |  | FLZ  150 mg/day,1w |  |  | N=30 |
| **Week:** | **-1** | **0** | **1** | **12** | **24** |
|  | Screening | Inclusion/  Baseline  Randomization | Follow-up | Follow-up | Follow-up and end of treatment |

##

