### Drop-outs

Differences in drop-out rates across treatment arms and baseline characteristics will be analyzed using Mann Whitney U test. Efficacy and safety will be analyzed for all randomized patients (i.e. intent-to-treat ITT). Additionally, we will also examine efficacy for the per-protocol (PP) population. We will examine the difference in dropout rates and missing visits across treatment arms.

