## Sample size calculations

The sample size and calculated power for the primary outcome of negative cultures for *Candida albicans* is based on data in Alvendal et al. Acta Obstet Gynecol Scand. 2017. In that study there was 100% positive cultures for *Candida albicans* before routine treatment with fluconazole for RVVC. After fluconazole treatment, 14% participants were still culture positive, with 86% success rate of primary outcome. Using the presumption: α= 5% β= 90%, success for routine FLZ treatment= 86%, success for experimental treatment with CHG in the current study= 86% with non-inferiority limit= 30%, 46 participants are needed (23 in each group) to achieve a power of 90 % not to exclude an effect-size of 30%. 60 participants will be included in case of drop-outs. All test will be performed at the 5% significance level.

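### The per-protocol set has no stated role in the non-inferiority decision, so an ITT pass with a per-protocol fail would still support the claim

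*Protocol*

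**What the plan says.** The section on overall study design states: "The study is a randomized open non-inferiority trial with parallel treatment groups". Section 10.4 enters "non-inferiority limit= 30" per cent into the sample size calculation.

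Two places rank the analysis sets. Section 10.2.1 puts treatment efficacy in all randomised women and continues: "Additionally, we will also examine efficacy for the per-protocol (PP) population". Section 10.2.2 repeats the order: "Efficacy and safety will be analyzed for all randomized patients (i.e. intent-to-treat ITT", again followed by the per-protocol set as an addition. Section 10.1, on the analysis population, gives only the numbers randomised.

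No sentence says that the per-protocol result must meet the limit, or what follows if the two sets disagree. The only definition of per-protocol is in the abbreviation list. It requires completion of the whole study with no deviation of any kind, although the primary endpoint is the culture 1 week after active treatment.

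**The concern.** In a superiority trial, analysing all randomised women is usually cautious, because non-adherence tends to dilute a benefit. In a non-inferiority trial the same dilution can favour the claim. If women who do not take their allocated drug respond alike in both arms, they pull the two clearance rates together and a real deficit looks smaller.

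Both treatments are dispensed by pharmacies and self-administered at home, with adherence followed at visits and in a weekly diary, so full adherence cannot be taken for granted. At stake is whether a cream that is 30 points worse in women who use it could be declared non-inferior more often than the planned error rate suggests, while a per-protocol analysis that would have shown this carries no weight.

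**Working it through.** **Inputs from the protocol.** Fluconazole success 86%, CHG success 86%, limit 30 points, α 5%, power 90%, 23 per group needed, 60 randomised (30 per arm): all from section 10.4. Section 10.2.1 specifies 95% confidence intervals.

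**The plan's own figure.** n per group = (z₁₋α + z₁₋β)² × 2 × 0.86 × 0.14 / 0.30².
- One-sided 5%: (1.645 + 1.282)² × 0.2408 / 0.09 = 22.9, so 23 per group and 46 in all. This matches the protocol.
- One-sided 2.5%, which is what a two-sided 95% interval implies: 28.1, so 29 per group. This does not match.

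Because the protocol supports either level, results are given for both a 95% and a 90% interval.

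**Assumptions, not in the protocol.** Adherent women clear at 86% (fluconazole) and 56% (CHG, exactly at the limit). Non-adherent women clear at 30–50% in either arm. Non-adherence is 10–20% where equal. The interval is Newcombe's, since the protocol names none for a difference in proportions.

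**Shrinkage with equal non-adherence q.** ITT deficit = (1 − q) × 30.
- q = 10%: 0.90 × 30 = 27 points.
- q = 20%: 0.80 × 30 = 24 points.

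**Unequal non-adherence.** Each arm's ITT rate = (1 − q) × adherent rate + q × non-adherent rate.
- Cream 20%, fluconazole 5%, non-adherers at 30%: CHG 0.80 × 56 + 0.20 × 30 = 50.8%; fluconazole 0.95 × 86 + 0.05 × 30 = 83.2%; deficit 32.4 points. With non-adherers at 50% it is 84.2 − 54.8 = 29.4 points.
- Cream 10%, fluconazole 20%: 74.8 − 53.4 = 21.4 points (non-adherers at 30%) or 78.8 − 55.4 = 23.4 points (at 50%).

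**Chance that ITT alone passes** (lower limit for CHG minus fluconazole above −30 points; 30 per arm; exact binomial enumeration):

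| Non-adherence, cream / fluconazole | 95% interval | 90% interval |
|---|---|---|
| 0 / 0 | 2.9% | 5.7% |
| 10% / 10% | 5.4–5.6% | 9.5–9.7% |
| 20% / 20% | 9.3–9.8% | 15.0–15.4% |
| 20% / 5% | 1.9–3.4% | 3.7–6.4% |
| 10% / 20% | 10–14% | 16–21% |

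Relative to full adherence, the equal cases are 5.4/2.9 = 1.9 to 9.8/2.9 = 3.4 times as high (95%), or 9.5/5.7 = 1.7 to 15.4/5.7 = 2.7 times (90%). A Wald interval gives a smaller rise in the equal cases: 4.5–7.4% against 2.7% (95%), and 8.1–12.6% against 5.0% (90%).

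**Requiring both sets** (200,000 simulated trials per scenario, equal non-adherence, per-protocol set = adherers): the pass rate returns to 2.5–2.7% (95%) or 4.8–5.1% (90%). At 20% equal non-adherence, 6.7–7.3% of trials (95%) pass ITT but fail per-protocol. With cream 10% and fluconazole 20%, the joint rule gives about 3% (95%).

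**The case against.** **The rule may be in the SAP.** Per-protocol efficacy is planned and stated twice, and section 10.2.1 never ties the non-inferiority conclusion by name to one set. The SAP is listed as an attachment and was not available. This stands in part: a reader should not infer that the safeguard is absent. But the protocol itself ranks the sets, twice, and that ranking is what needs correcting.

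**The direction is not given.** A reader might infer that ordinary non-adherence inflates the error two- to four-fold. The protocol does not support that as a general statement. It gives no adherence rate, and the arms carry different burdens: seven nightly vaginal applications with some leakage, against three capsules of a regimen that the protocol expects most participants to know already. Worse adherence to the cream removes or reverses the inflation, as the table shows. This objection stands, and the point is conditional for that reason.

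**ITT is not invalid.** A reader might also infer that the 5% error rate holds only if adherence is near complete. It does not depend on that. ITT keeps its error rate for the effect of assignment; in the equal scenarios that effect really is 24–27 points, inside the limit. The inflated rates concern a different quantity, the effect among women who take the drug.

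**Per-protocol brings its own bias.** The abbreviation-list definition selects on the whole 24 weeks and could drop women for whom the cream failed or irritated. This stands too. It argues against replacing ITT with per-protocol, not against requiring both.

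**Conclusion.** The point holds in conditional form. The protocol makes ITT the efficacy analysis of a non-inferiority trial and gives the per-protocol set no part in the decision. If non-adherence is similar in the two arms (assumed 10–20%, non-adherers clearing at 30–50%), ITT alone passes a cream at the limit about 2 to 3 times as often as under full adherence. The excess is larger if fluconazole adherence is the worse, and small, absent or reversed if cream adherence is the worse. Which case applies cannot be read from the protocol, and that is the reason to fix the decision rule before results are known. It is a worthwhile tightening, not a fatal flaw.

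**What to change.** Add to section 10.2.1: *Non-inferiority on the Visit 3 culture is concluded only if the lower confidence limit for CHG minus FLZ is above −30 percentage points in both the ITT set and the per-protocol set. The per-protocol set for this endpoint is defined by deviations up to the Visit 3 culture. If the sets disagree, non-inferiority is not concluded.*

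**Cost.** No extra patients or data. With both drugs truly at 86% and equal non-adherence, power changes as follows:
- 10% non-adherence: from 84–86% to 80–82% (95% interval), or from 91–93% to 89–90% (90% interval).
- 20% non-adherence: from 79–82% to 73–76%, or from 87–90% to 83–85%.

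That is about 2–6 points, and it depends on limiting the per-protocol set to deviations up to Visit 3. If the whole-study, zero-deviation definition were kept and removed 30–40% of women at random (an assumption), joint power would fall from 90% to 69–76% (95%) or from 95% to 80–85% (90%). The definition therefore has to change together with the rule.

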# Subject selection

## Inclusion criteria

To be included in the study, subjects must meet the following criteria:

- 18-50 years of age
- A history of > 2 candida infections the last year
- Symptoms of acute vulvovaginal candida infection
- Culture verified infection with *Candida albicans*
- Adequate contraceptive method
- Able to understand oral and written information in Swedish
- The subject has given written consent to participate in the study

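### The interval methods named in section 10.2.1 do not match the 30-point risk difference on which the non-inferiority limit and N = 46 rest, and no section sets a confidence limit against that limit

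*Protocol*

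**What the plan says.** Section 10.4 (Sample size calculations) sets the design values: "α= 5% β= 90%, success for routine FLZ treatment= 86" per cent, the same 86% for chlorhexidine (CHG), and "with non-inferiority limit= 30" per cent. It concludes that 23 women per group are needed and raises the total from 46 to 60 for drop-outs. It closes with "All test will be performed at the 5% significance level", without saying whether tests are one-sided or two-sided.

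Section 10.2.1 (Statistical methods) states that differences in means, proportions and medians will be examined with 95% confidence intervals. The next sentence says how: "The CI interval will be computed using 1) for a proportion in one sample and 2) logistic or multinomial logistic regression analysis". The same paragraph says "Four time points will be used to study the efficacy" in each treatment arm and lists baseline as the first of them. The primary endpoint, however, is a single time point, 1 week after active treatment.

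Section 6.1 (Inclusion criteria) requires "Culture verified infection with" *C. albicans*, and the visit description places randomization after the positive culture.

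**The concern.** A non-inferiority claim needs three matching parts: a limit on a stated scale, an interval on that scale, and a rule that compares the two. The protocol has the first. The methods it names for the second work on other scales by default. A one-sample interval describes one arm and gives no interval for a difference. Logistic regression reports an odds ratio, and a 30-point loss has no fixed odds-ratio equivalent. The third part appears nowhere in section 10.

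This is more than detail left to the SAP, because the protocol names interval methods. An SAP that follows them inherits the mismatch, and one that corrects them departs from the protocol. In an open trial, an unsettled scale for the single confirmatory claim also leaves room to choose the scale after the results are seen.

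**Working it through.** **Inputs.** From section 10.4: success 0.86 in both arms, limit 0.30, alpha 5%, power 90%, 23 per group, 60 enrolled. From section 10.2.1: 95% intervals. The 1:1 ratio is in the Randomization section. Alpha is not given a side, so both readings are tried. Section 10.4 labels the 90% as β, but its own wording, "to achieve a power of 90 % not to exclude an effect-size of 30" per cent, shows that power is meant.

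**1. Reproducing N = 46.** For an absolute risk difference, n per arm = (z₁₋α + z_power)² × 2p(1−p) / limit².
- One-sided 5%: (1.645 + 1.282)² × 2(0.86)(0.14) / 0.30² = 22.9, so 23 per arm and 46 in total. This matches.
- One-sided 2.5% (a two-sided 95% interval): (1.960 + 1.282)² × 0.2408 / 0.09 = 28.1, so 29 per arm and 58 in total.
- Limit read as relative (0.30 × 0.86 = 25.8 points): 62 at one-sided 5% and 78 at one-sided 2.5%.

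Of these readings, only an absolute 30-point between-arm difference at one-sided 5% gives 46.

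**2. The limit on the odds-ratio scale.** At 86% control success, 30 points lower is 56%: (0.56/0.44) / (0.86/0.14) = 1.273/6.143 = 0.207. The protocol gives only the 86% control rate, so the other rates below are assumptions that show the range.

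| Assumed FLZ success | OR equal to a 30-point loss | Loss allowed by a fixed OR of 0.207 |
|---|---|---|
| 75% | 0.273 | 36.7 points |
| 80% | 0.250 | 34.7 points |
| 86% | 0.207 | 30.0 points |
| 90% | 0.167 | 24.9 points |
| 95% | 0.098 | 15.3 points |

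No single odds-ratio limit stands in for 30 points.

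**3. One data set, two conclusions.** Suppose 26/30 are negative on CHG and 29/30 on FLZ.
- Risk difference: 0.867 − 0.967 = −0.100. The Wilson 95% intervals are 0.703 to 0.947 (CHG) and 0.833 to 0.994 (FLZ). Newcombe lower limit: −0.100 − √[(0.867 − 0.703)² + (0.994 − 0.967)²] = −0.266. The upper limit is +0.056. The lower limit is above −0.30, so CHG is non-inferior.
- Odds ratio: (26 × 1)/(4 × 29) = 0.224, with SE of the log = √(1/26 + 1/4 + 1/29 + 1/1) = 1.150. The lower limit is exp(−1.495 − 1.96 × 1.150) = 0.024, which fails against 0.207. It also fails if the 30 points are converted at the observed FLZ rate: (20/10)/(29/1) = 0.069.
- The two one-sample intervals alone give no interval for the difference.

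**4. Power with 30 per arm, true success 86% in both, 95% interval.** Enumerating all outcomes, a Newcombe risk-difference interval against −0.30 has power 90.0%. A Wald odds-ratio interval against 0.207 has about 55% (56% by normal approximation).

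**5. Confidence level.** By the protocol's own formula, power is Φ(0.30/√(0.2408/n) − z₁₋α).

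| n per arm | One-sided 5% | Two-sided 95% interval |
|---|---|---|
| 23 | 90.1% | 83.5% |
| 30 | 95.6% | 91.8% |

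**6. Baseline.** Every randomized woman is culture-positive, so the baseline proportion negative is 0% in both arms. It carries no information on the arm comparison.

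**The case against.** The strongest reply is that the intent is already there: section 10.2.1 does announce 95% intervals for a difference in proportions, and logistic regression can deliver one. With arm as the only term at one visit, the fitted probabilities equal the observed proportions, and the delta method gives a risk-difference interval. For 26/30 versus 29/30 it is −0.238 to +0.038, with SE 0.0702, the unpooled form that also reproduces N = 46. The exact interval method and the wording of the decision rule are commonly left to the SAP, which is listed as an attachment and is not at hand.

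Much of this stands. The announced difference is not tied to the primary endpoint, the two arms or the limit, however, and the conversion from odds ratio to risk difference is not stated. What remains is a named method whose default output is on another scale from the limit.

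Two stronger readings are tempting. A reader might infer that the trial cannot answer its primary question. It can, because the data allow a risk difference and the named model can be converted to one. A reader might also infer that the four-time-point analysis is one logistic model with infinite estimates from the 0% baseline and with repeated results treated as independent. The protocol specifies no such pooled model. Its wording refers to each arm, which fits a description by visit with one-sample intervals.

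**Conclusion.** The mismatch is real and concerns the trial's single confirmatory claim. Section 10.4 rests on an absolute between-arm difference. Section 10.2.1 names methods that by default give per-arm intervals and odds ratios, and nothing links a confidence limit to the 30-point limit. The choice of scale can reverse the conclusion on the same data, and at 30 per arm it moves power from about 90% to about 55%.

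These figures assume 86% success in both arms, full follow-up of 60 women, a 95% interval, and an odds-ratio limit converted at 86%. The protocol does not itself propose 0.207; it is what a reader would need in order to use the odds ratio. Separately, the 95% level in section 10.2.1 does not match the one-sided 5% behind N = 46. The conclusion goes no further than the protocol text as written, and an SAP might already state a matching analysis.

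**What to change.** - **Primary analysis (section 10.2.1).** For the primary endpoint, replace the sentence on interval computation with a confidence interval for the difference in proportions negative (CHG minus FLZ) at Visit 3. Use a score-type method such as Newcombe or Miettinen-Nurminen, or a risk difference derived from the logistic model. Declare non-inferiority only if the lower limit is above −30 points.
- **Level (sections 10.2.1 and 10.4).** State whether the decision uses a two-sided 95% interval or a one-sided 5% test, and restate the sample size to match. With the 95% interval, 58 evaluable women are needed for 90% power, so 60 enrolled leaves room to lose two. With one-sided 5%, 46 stands, but the decision interval is then a two-sided 90% one.
- **Over-time efficacy.** Show baseline culture status descriptively only. If one model is fitted over visits, use the post-baseline visits and account for correlation within a woman.

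The change of method costs a few sentences in the protocol and the SAP and needs no new data. Choosing the 95% level also uses up nearly all of the drop-out allowance, and that should be said openly.

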## Secondary endpoint (variables)

1. The proportion of women in each group that has negative vaginal cultures for *Candida albicans* at 3 months’ follow-up after prophylactic treatment and at 6 months’ follow-up after the observational phase of the study.
2. Analysis of proportion of women with adverse events (AE) across treatment arms. The AEs will also be reported in descriptive terms and summarized for each treatment arm.
3. Proportion of women with symptom score > 2. Each symptom of typical discharge, itching, dryness of the skin/mucosa, burning and pain will generate 1 point of a composite index (range 0-5).
4. Proportion of women with examination score >2. Each finding of redness skin/mucosa, typical discharge, dry skin/mucosa, fissures skin/mucosa, visible candida hyphae in the microscope will generate 1 point of a composite index (range 0-5).
5. Proportion of women with reduced vaginal lactobacilli content in vaginal smears measured by a semi-quantitative method as normal or reduced quantity.
6. Proportion of women with relapse of *Candida albicans* infection between end of treatment and end of prophylactic treatment (1week post treatment to 3 months’ follow-up) and between 3- and 6 months’ follow-up after end of prophylactic treatment.
7. Proportion of women with possible toxic effect on the vaginal epithelium, defined as disruption and/or inflammation of the epithelial lining, analyzed from vaginal biopsies before and after treatment and prophylaxis.
8. Further analysis of mucosa inflammatory mechanism (histopathology and immunohistochemistry) and biofilm formation during and after treatment and prophylaxis, analyzed from vaginal biopsies. The methods for these *in vitro* exploratory analyses are not yet decided on.

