## Methods for measurement of endpoints (variables) for clinical safety

Two of the secondary endpoints are used for clinical safety;

1. Adverse events will continuously be registered during the study. The participants can fill out any AE in a web based digital diary and also contact the research midwife when needed. AEs will be registered in the CRF. AEs will be analyzed as proportion of women with AE and compared across study arma. For more details, see section 9.
2. Possible toxic effects on the vaginal cells after CHG treatment will be analyzed in vaginal biopsies described under 8.1.2. The analysis will focus on injuries of the epithelial lining and increase of inflammatory and immunological markers (antimicrobial peptides, cytokines, kemokins, CIDAMP). The biopsies will be taken at inclusion and at 3 months’ follow-up, when the prophylactic phase of the study is completed. Biopsies from participants allocated to FLZ will serve as controls.

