# Statistics

## Analysis population

The study is a RCT controlled non-inferior trial with 60 women randomly assigned to either vaginal chlorhexidine gluconate (N=30) or oral fluconazole (N=30). Baseline plus 3 follow-up visits (baseline/inclusion, 1 week, 3 months and 6 months) are planned.

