## Statistical analyses

### Statistical methods

***Objective:*** The aim of this study is to analyze whether vaginal chlorhexidine gluconate (CHG) is at least as effective and safe as oral fluconazole (FLZ) as treatment and prophylaxis for recurrent vulvovaginal candidiasis.

***Study design:*** Randomized controlled non-inferior trial with 60 women randomly assigned to either vaginal chlorhexidine gluconate (N=30) or oral fluconazole (N=30). Baseline plus 3 follow-up visits (baseline/inclusion, 1 week, 3 months and 6 months) are planned.

***Primary outcome****:* Proportion of women with negative cultures for *Candida albicans* 1week post-treatment.

***Secondary outcomes****:*

- Negative cultures for *Candida albicans* at 3 months’ and 6 months’ follow-ups, after end of prophylactic treatment.
- Analysis of proportion of women with adverse events (AE). The AEs will also be reported in descriptive terms and summarized for each treatment arm.
- Proportion of women with symptom score > 2. Each symptom of typical discharge, itching, dryness of the skin/mucosa, burning and pain will generate 1 point of a composite index (range 0-5).
- Proportion of women with examination score >2. Each finding of redness skin/mucosa, typical discharge, dry skin/mucosa, fissures skin/mucosa, visible candida hyphae in the microscope will generate 1 point of a composite index (range 0-5).
- Proportion of women with reduced vaginal lactobacilli content in vaginal smears measured by a semi-quantitative method as normal or reduced quantity.
- Proportion of women with relapse of *Candida albicans* infection between end of treatment and end of prophylactic treatment (1week post treatment to 3 months’ follow-up) and between 3- and 6 months’ follow-up after end of prophylactic treatment.
- Proportion of women with possible toxic effect on the vaginal epithelium, defined as disruption and/or inflammation of the epithelial lining, analyzed from vaginal biopsies before and after treatment and prophylaxis.
- Further analysis of mucosa inflammatory mechanism and biofilm formation during and after treatment and prophylaxis, analyzed from vaginal biopsies. The methods for these *in vitro* exploratory analyses are not yet decided on.

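### Section 10.2.1 promises differences in proportions but names only logistic regression to compare the arms, a model that gives odds ratios and has no finite estimate when one arm has no events

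*Protocol*

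**What the plan says.** The effect measure is fixed in section 10.2.1, Statistical methods: "We will examine the difference in means, proportions and median values using 95% confidence intervals (CI". The methods follow at once: "The CI interval will be computed using 1) for a proportion in one sample and 2) logistic or multinomial logistic regression analysis". The section does not say whether logistic inference is to be Wald, score, likelihood-ratio or penalised.

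The outcomes covered are listed at the head of the same section: "Analysis for differences over time for treatment efficacy, AEs, symptom- and examination score, impact on vaginal lactobacilli and relapses will be analyzed for all randomized". Relapse is a proportion: "Proportion of women with relapse of *Candida albicans* infection between end of treatment and end of prophylactic treatment". Epithelial toxicity is also a binary secondary endpoint, "Proportion of women with possible toxic effect on the vaginal epithelium, defined as disruption and/or inflammation of the epithelial lining", but it is not in that list. Section 8.2 makes it one of two safety endpoints and adds: "Biopsies from participants allocated to FLZ will serve as controls".

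The other tests named serve other purposes. Chi-square is for baseline comparisons ("Differences in baseline characteristics between the CHG and FLZ groups will be analyzed with Chi2 for categorical data"), and Mann-Whitney is for ordinal baseline data and drop-out. The trial has "60 women randomly assigned to either vaginal chlorhexidine gluconate (N=30) or oral fluconazole (N=30". Section 10.3 sends the p-values of all secondary outcomes through a false-discovery-rate adjustment.

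Section 10.2.1 also counts baseline among the four time points for culture negativity, while the inclusion criteria require a culture-verified infection.

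**The concern.** There are two problems in one sentence of the plan.

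First, the effect promised and the method named do not match. A logistic model returns an odds ratio. The plan gives no route from there to an interval for a difference in proportions.

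Second, the named model fails with an empty cell, and arms of 30 can produce one for an uncommon outcome. Events on the cream and none on fluconazole is a pattern that the safety comparison should be able to describe. With that pattern the odds ratio is infinite, and a Wald p-value near 1 could enter the false-discovery-rate step. Whether that happens depends on a choice of test that the protocol leaves open.

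**Working it through.** **Inputs.** From the protocol: 30 women per arm, binary secondary outcomes, 95% intervals, 5% level, 86% success and a 30-point margin. The protocol expects no particular rate of toxicity, adverse events or relapse, so the counts and rates below are assumptions.

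**The plan's own scale.** The sample size in section 10.4 is computed on the difference in proportions. With one-sided 5% and 90% power, n = (1.645 + 1.282)² × 2 × 0.86 × 0.14 / 0.30² = 22.9, so 23 per arm and 46 in total, as stated.

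**An empty arm, 6/30 against 0/30 (illustration).**
- *Wald test, logistic model.* No finite maximum exists. Three fitting routines gave log odds ratios of 22.2, 19.3 and 19.2, with standard errors of 14,508, 5,720 and 3,237. The p-values run from 0.995 to 0.999.
- *Likelihood-ratio test, same model.* G² = 2[6 ln(0.2/0.1) + 24 ln(0.8/0.9) + 30 ln(1/0.9)] = 2(4.159 − 2.827 + 3.161) = 8.99, p = 0.0027. The profile interval for the odds ratio starts at 3.1 and has no upper limit.
- *Score test.* 0.2² / (0.1 × 0.9 × 2/30) = 6.67, p = 0.0098.
- *Fisher's exact test.* 2 × C(30,6)/C(60,6) = 2 × 593,775/50,063,860 = 0.024.
- *Firth-penalised logistic.* Odds ratio 16.2 (95% CI 1.8 to 2150), p = 0.009.
- *Newcombe interval.* The Wilson limits are 0.095 to 0.373 and 0 to 0.1135. The lower limit is 0.2 − √(0.105² + 0.1135²) = 0.045 and the upper is 0.2 + (0.373 − 0.2) = 0.373. The difference is 20.0 points (4.5 to 37.3).
- *Miettinen-Nurminen interval.* At a difference of 0.0737 the constrained rates are 0.1040 and 0.0303. The variance is (0.1040 × 0.8960 + 0.0303 × 0.9697)/30 × 60/59 = 0.00415, and (0.2 − 0.0737)²/0.00415 = 3.84. So the lower limit is 7.4 points; the upper, found the same way, is 37.5.

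The Wald result does not depend on the size of the other count. At 10/30 against 0/30 it is still p = 0.999, with Fisher at 0.0008 and likelihood-ratio at 0.00007. With one event in the sparse arm (6/30 against 1/30) the Wald fit converges, p = 0.076.

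**How likely is an empty arm?** The chance is (1 − rate)^30: 74% at 1%, 55% at 2%, 21% at 5%, 4% at 10% and 1.1% at 14%. The last rate is the share still culture-positive after fluconazole in the study cited in section 10.4.

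**What the choice of test costs.** Exact enumeration at 30 per arm, assuming true rates of 20% against 2% and counting tables with an empty arm as non-significant for Wald, gives this power: Wald 15%, Fisher 41%, Newcombe interval 56%, score about 70%, likelihood-ratio 74%. The likelihood-ratio test is somewhat liberal here (size 6–8%); the score test is not materially so (3–5%).

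**An empty cell by design.** Culture negatives at baseline are 0/30 in both arms. Assume week-1 clearance of 26/30 on fluconazole and 12/30 on chlorhexidine, and fit arm, time and their interaction with baseline as reference, ignoring within-woman correlation. The interaction has a standard error of about 34,000 and Wald p = 1.000. Fisher on the week-1 counts gives 0.0004.

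**The case against.** The strongest reply is that the protocol names a model, not the Wald test. Likelihood-ratio and score tests from that same model keep the signal in the 6/30 against 0/30 example (p = 0.003 and 0.010) and have more power than Fisher. A reader might infer that a toxicity or relapse signal of this kind would be reported as p of about 1. The document does not support that: it holds only under Wald inference, which is common by default but not specified here.

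Other parts of the reply also stand:
- Toxicity is outside the outcome list in section 10.2.1. Logistic regression applies to it only by inference, because no other between-arm method is given. For adverse events and relapse it applies directly.
- The low rates are assumptions. The background section calls relapse risk high, and inflammation of the epithelium is not specific to a cream.
- Separate one-sample intervals are planned. With exact limits they would show 8–39% against 0–12%, and a standard error in the thousands is a visible fitting failure. So a real harm need not pass unnoticed.
- A per-visit analysis avoids the baseline problem, and the protocol does not exclude one.

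The last argument is that a sparse-data fallback belongs in the statistical analysis plan, which is listed as an attachment but not shown. Taken alone, that is right. But the protocol itself promises one effect measure and fixes a method that yields another, and a plan that follows it inherits the mismatch. Nor does a likelihood-ratio test make the odds ratio finite or close its interval.

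**Conclusion.** The point holds in a limited form. Section 10.2.1 fixes, as its only between-arm method for outcome proportions, a model that does not give the promised difference and has no finite estimate when an arm is empty. That follows from the text and the algebra and needs no assumption about rates.

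How much it matters does depend on assumptions. Under Wald inference an empty arm gives p near 1 whatever the other count; under likelihood-ratio or score inference the test survives but the maximum-likelihood odds ratio stays infinite. An empty arm is likely only for uncommon outcomes, roughly 5% or less, and unlikely at 10% or above. The baseline problem arises only if all four time points are modelled together with baseline as reference and Wald inference is used. It should not be inferred that the plan is bound to hide a harm, nor that logistic regression as such loses the signal.

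**What to change.** In section 10.2.1:
1. Compare binary secondary outcomes at each visit or window by the risk difference with a Miettinen-Nurminen (score) or Newcombe 95% interval.
2. Take the p-value for the false-discovery-rate step from one pre-named test that suits the interval, for example the score test with Miettinen-Nurminen. Fisher's test is valid but conservative and can disagree with Newcombe: at 5/30 against 0/30 the Newcombe lower limit is +2.0 points while Fisher gives p = 0.052.
3. Where a model is needed, use Firth-penalised logistic regression, or likelihood-ratio tests with profile-likelihood intervals, instead of Wald.
4. Do not fit baseline culture as an outcome time point.
5. State that the method also covers epithelial toxicity.

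The cost is a change of wording and a few lines of code. Sample size, visits and data collection are unaffected.
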